# 6. Study drug

## 6.1 Name of study drug, components, contents, dosage form, etc.

(1) Name of study drug

Test drug: NIK-333

(2) Chemical name

（2*E*,4*E*,6*E*,10*E*）-3,7,11,15-Tetramethylhexadeca-2,4,6,10,14-pentaenoic acid

(3) Structural formula

Molecular formula: C20H30O2

Molecular weight: 302.45

(4) Content and dosage form of the study drug

Test drug: NIK-333

Yellow-brown soft capsules containing 75 mg of the active component in one capsule

(5) Stability of the study drug

The study drug was stable for 36 months in the long-term storage study (25°C, 60%RH) and for 6 months in the accelerated study (40°C, 75%RH). The expiration date will be 3 years (36 months) from the date of production of the study drug.

## 6.2 Packaging and labeling of the study drug

(1) Packaging

The study drugs are provided in PTP package containing 10 capsules per sheet. Ten sheets of PTP package are put in an aluminum bag, and one aluminum bag is placed in a small box. Fifteen small boxes are put in a large box.

(2) Labeling

The following information will be indicated on the label.

[1] The fact that it is an investigational drug

[2] Name and address of the sponsor

[3] Identification code and batch number

[4] Number of capsules

[5] Storage method

[6] Expiration date

(3) Storage condition

The PTP package will not be opened and will be kept at room temperature until the time of administration of the study drug.

## 6.3 Management of study drugs

(1) Delivery of the study drug

The sponsor will deliver the study drug directly to the study drug storage manager of the study center after the study contract has been signed by the sponsor and the study center. The sponsor will prepare the manual for study drug management and submit it to the head of the study center.

(2) Storage and management of the study drug

The study drug storage manager will properly manage and store the study drug according to the above-described manual for study drug management, and will prepare study drug management records to identify the status of the use of the study drug.

(3) Collection of the study drug

The sponsor will collect leftover study drugs, empty boxes and unused study drugs together with the study drug management record (copy) for the subjects at an appropriate timing.

# 7. Examination and observation parameters

## 7.1 Procedures of subject registration

(1) Informed consent and definite diagnosis

[1] Informed consent from the subjects

The investigator or the subinvestigator will evaluate patients who have undergone topical medical therapy or surgical resection, and obtain informed consent in writing from those patients deemed eligible to participate in this study.

[2] Confirmation of eligibility of the subjects

After an informed consent has been obtained from a subject, the investigator or the subinvestigator will perform the scheduled dynamic CT and various tests to confirm complete cure within 56 days before registration, and will confirm that the subject satisfies the inclusion criteria and does not fall under any exclusion criteria.

[Test parameters regarding the inclusion criteria and exclusion criteria]

1） Dynamic CT images

2） Medical examination (symptoms/signs)

3） Blood pressure (dorsal position or sitting position)

4） Child Pugh classification

(Liver encephalopathy, ascites, serum bilirubin, serum albumin and prothrombin time)

5) HCV-RNA tests (quantitative)

6) HBs antigen tests (qualitative)

7） HCG tests (pregnant or not: premenopausal women only)

8） Hematology tests (platelet count, hemoglobin level)

(2) Subject registration

The investigator or the subinvestigator will enter necessary information on the subject registration form and will fax it to the subject registration center. The sponsor will confirm on the subject registration form received (Fax) that there are no problems in the eligibility of the subjects.

(3) Study drug assignment and start of study drug administration

The investigator or the subinvestigator will start administration of the study drug according to the assignment table prepared in advance.

## 7.2 Preparation of subject screening name list, etc.

The investigator or the subinvestigator will prepare a tabulated list (subject screening name list) of those patients who have received briefing about the contents of the study using written information for informed consent. Record the day on which the information regarding the study is given, the day on which informed consent is obtained, and the day on which study drug administration is started on the subject screening name list.

## 7.3 Subject backgrounds

Record the information listed below for the subjects for whom registration confirmation forms have been sent.

[1] Subject number

[2] Before complete cure: As of the time of diagnosis of HCC [the date and procedure of CT examination, diameter of the main tumor, number of tumors, first occurrence/first recurrence (timing of treatment of first occurrence in the case of first recurrence)]

[3] Radical therapy: Date of treatment, operative procedure for treatment (treatment method in the case of topical medical therapy), and the date of CT examination for confirmation of complete cure

[4] Previous history and complications

[5] Results of the tests on registration

[6] Information regarding registration (date of subject registration, date of informed consent, date of birth, gender)

[Flow of registration]

Subjects will be registered according to the following flow.

|  | 8 weeks (56 days) or more and 12 weeks (84 days) or less | 8 weeks (56 days) or less |  |
| --- | --- | --- | --- |

| Subjects |  |  |  |  |  |  |  |  |  |  |  |  |  |  |  |  |  |  |  |  |  |  |  |  |
| --- | --- | --- | --- | --- | --- | --- | --- | --- | --- | --- | --- | --- | --- | --- | --- | --- | --- | --- | --- | --- | --- | --- | --- | --- |
| Hepatocellular carcinoma of first occurrence or first recurrence | |  | Topical medical therapy or surgical resection |  |  |  |  | Briefing to subjects |  | Obtaining subjects’ consent |  |  |  |  |  |  |  |  |  |  |  | Liver biopsy/start of study drug administration |  |
|  |  |  |  |  |  |  |  |  |  |  |  |  |  |  |  |  |  |
|  |  |  |  |  |  |  |  |  |  |  |  |  |  |  |  |  |  |  |  |
| Investigator  or  Subinvestigator |  |  |  |  |  |  |  |  |  |  |  |  |  |  |  |  |  |  |  |  |
| Diagnosis | |  |  | Diagnosis (postoperative confirmation) | |  |  |  | Definite diagnosis | | | |  |  |  | Registration/confirmation of assignment | |  |  |
|  |  |  |  |  |  |  |  |  |  |
|  |  |  |  |  |  |  |  |  |  |  |  |  |  |  |  |  |  |  |  |  |  |  |  |
| Kowa Company, Ltd.  Pharmaceutical Development 2 |  |  |  |  |  |  |  |  |  |  |  |  |  |  |  |  |  |  |  |  |  |  |  |  |
|  |  |  |  |  |  |  |  |  |  |  |  |  |  | Confirmation of eligibility | |  | Subject registration |  | Assignment | |  |  |  |
|  |  |
|  | | | | | | | | | | | | | | | | | | | | | | | | |

[Study schedule]

Conduct examination/observation/investigation upon subject registration and during the study drug administration period according to the following schedule.

| Timing (week)  Parameter | | Registration (within 56 days before) | During study drug administration period | | | | | | | At the time of follow-up examination (Week 12 after completion of study drug administration) | At the time of study discontinuation |
| --- | --- | --- | --- | --- | --- | --- | --- | --- | --- | --- | --- |
| Start of administration  (within 14 days before) | Weeks 4, 28, 52, 76 | Weeks 8, 32, 56, 80 | Weeks 12, 36, 60, 84 | Weeks 16, 40, 64, 88 | Weeks 20, 44, 68, 92 | Weeks 24, 48, 72, 96 |
| Study drug administration | |  |  | | | | | | |  |  |
| Examination of compliance status | |  |  | ● | ● | ● | ● | ● | ● |  |  |
| Gene expression profile | |  |  |  |  |  |  |  |  |  |  |
| TGF- | |  |  |  |  | ● |  |  | ● |  |  |
| Liver drug concentration | |  |  |  |  |  |  |  |  |  |  |
| Plasma drug concentration | |  |  |  |  |  |  |  | ● | ● |  |
| Urinary drug concentration | |  |  |  |  |  |  |  |  |  |  |
| Abdominal imaging diagnosis | | ● |  |  |  | ● |  |  | ● | ● |  |
| Medical examination | | ● | ● | ● | ● | ● | ● | ● | ● | ● |  |
| Vital signs, etc. | | ● | ● | ● | ● | ● | ● | ● | ● | ● |  |
| Child-Pugh classification | Encephalopathy/ascites | ● |  |  |  |  |  |  |  |  |  |
| T-Bil, ALB, PT | ● |  |  |  |  |  |  |  |  |  |
| HBs antigen | | ● |  |  |  |  |  |  |  |  |  |
| HCG tests (premenopausal women only) | | ● |  |  |  |  |  |  | ● |  |  |
| Hematology tests  (platelet count, hemoglobin level) | | ● |  |  |  |  |  |  |  |  |  |
| Hematology tests | |  | ● | ● | ● | ● | ● | ● | ● | ● |  |
| Blood biochemistry tests | |  | ● | ● | ● | ● | ● | ● | ● | ● |  |
| Urinary tests (fresh urine) | |  | ● | ● | ● | ● | ● | ● | ● | ● |  |
| Blood pressure parameters | |  | ● |  |  |  |  |  |  |  |  |
| HCV-RNA (quantitative) | | ● |  |  |  |  |  |  |  |  |  |
| HCV-RNA (genotype analysis) | |  | ● |  |  |  |  |  |  |  |  |
| Tumor markers | |  | ● |  |  | ● |  |  | ● | ● |  |
| Fibrosis marker | |  | ● |  |  |  |  |  |  |  |  |
| Bone densitometry (DXA，lumbar vertebrae) | |  |  |  |  |  |  |  |  |  |  |
| Endoscopy | |  |  |  |  |  |  |  |  |  |  |
| ECG | |  |  |  |  |  |  |  | ● |  |  |
| Echocardiography | |  |  |  |  |  |  |  |  |  |  |
| Pulse wave examination | |  |  |  |  |  |  |  |  |  |  |
| Fundus examination | |  |  |  |  |  |  |  |  |  |  |
| Adverse events | |  |  | | | | | | | |  |

: The day before the start of administration and the day of evaluation at Week 8

: Examination will be conducted during the period between the end of radical therapy and the start of study drug administration.

: Examination will be conducted at 48-week intervals.

: Examination will be conducted upon discontinuation of the study if possible.

Note 1: The acceptable range of deviation from the scheduled examination, observation and evaluation during the study period is +28 days for gene expression profile (Week 8) and pharmacokinetics (Week 8); 35 days for abdominal imaging diagnosis, HCV-RNA, HCG tests, tumor markers, fibrosis markers, bone densitometry, endoscopy, ECG, echocardiography，pulse wave examination, and fundus examination; and 7 days for other parameters.

Note 2: Subjects need to be hospitalized on the day of the start of administration and on the day of evaluation at Week 8. Liver biopsy will be performed and blood samples and accumulated urine samples will be collected on the day before the start of administration, with administration of the study drug to start 24 hours after the operation. On the day of evaluation at Week 8, subjects will visit the hospital without taking the study drug, and undergo liver biopsy 4 hours after administration. Blood samples will be collected 4 and 8 hours after administration. Urine samples will be accumulated for 24 hours after administration.

Note 3: Blood pressure parameters will be assessed on the day of the start of administration and at Week 48 and Week 96 of administration. If the systolic blood pressure exceeds 140 mmHg or the diastolic blood pressure exceeds 90 mmHg in two or more consecutive tests, the parameters will be determined on the second or subsequent tests. Determination of creatinine clearance, one of the blood pressure parameters, under increased blood pressure will be conducted to the extent possible. Creatinine clearance will be determined using urine samples collected at home at the timings other than the day of the start of administration (i.e., Week 48 and Week 96 of administration, and examination of blood pressure parameters in the presence of increased blood pressure).

Note 4: See Table 1, Table 2 and Table 3 at the end of this document for details about the contents of the tests.

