| Related | Abdominal distension, Blood pressure increased, Urticaria, Abnormal sensation in eye, Hyperglycaemia, Duodenitis, Gastritis, Lip dry, Keratoconjunctivitis sicca, Oropharyngeal Pain, Malaise | 1 | 22 |
| Blood urine present,, Reflux oesophagitis, Hypertriglyceridaemia,  Gamma-glutamyltransferase increased | 2 |
| Headache | 3 |

List of adverse events in repeated administration (2)

| Dose | Causal relationship | Events | Number of events | Total |
| --- | --- | --- | --- | --- |
| 900 mg  (At the start n= 9)  * Discontinued during repeated administration | None | Vertigo, Abdominal pain upper, Joint swelling, Chest pain, Alanine aminotransferase increased, Aspartate aminotransferase increased, Blood lactate dehydrogenase increased, Varices oesophageal, Pyrexia, VIth nerve paralysis, Scar,Back pain, Protein urine, Oropharyngeal discomfort, Insomnia, Headache, Nausea | 1 | 23 |
| Nasopharyngitis | 6 |
| Related | Diarrhoea, Chapped lips, Abdominal pain upper, Retinal haemorrhage, Stomach discomfort | 1 | 26 |
| Dysgeusia, Abdominal pain, Protein urine present, Musculoskeletal stiffness | 2 |
| Urinary occult blood positive | 3 |
| Blood pressure increase | 4 |
| Headache | 6 |

Among the 9 subjects who moved on to repeated administration at Level 3, 1 subject was suspended from drug administration and 3 subjects were discontinued from the study due to increased blood pressure. In 1 subject who exhibited blood pressure increase, fundal haemorrhage was observed. However, the subject was placed on observation without requiring medical intervention.

The incidences of events suggesting the presence of effects on renal functions, such as protein urine and urinary occult blood, also increased as compared with Level 1 and Level 2. The numbers of subjects whose protein urine and urinary occult blood shifted to + or more after the start of repeated administration at each level are shown in the table below. Abnormal changes of protein urine and urinary occult blood after the start of repeated administration were also observed in subjects who showed no blood pressure increase, suggesting that NIK-333 affects renal functions.

Frequency of subjects exhibiting a shift to (+) after repeated administration at
each level

|  | Change  Dose | Level of change: From baseline | | | | |
| --- | --- | --- | --- | --- | --- | --- |
| None | 1 grade | 2 grades | 3 grades | 4 grades |

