## 4.9 Amount of urine collected and frequency of urine sample collection

Urine sample will be accumulated for 24 hours at the time of “4.7 Liver tissues collection (during hospitalization for liver biopsy),” on the day of evaluation at Week 48, on the day of evaluation at Week 96, and in the presence of increased blood pressure (if possible).

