The sponsor will determine the concentration of NIK-333-26, a presumed metabolite,in plasma using the plasma samples remaining after determination of unchanged NIK-333 and NIK-333 lipids form in plasma. However, the metabolite can be determined only when the subject’s additional consent has been obtained in advance. The chemical name and structural formula of the presumed metabolite are shown below.

- NIK-333-26

Chemical name: (6*E*,10*E*)-3,7,11,15-tetramethyl-6,10,14-hexadecatrienoic acid

Structural formula:

[6] Procedure of determination of the concentrations of metabolite

To determine the concentration of NIK-333-26, extract the remaining plasma samples, obtain derivatives and determine the concentrations in plasma by liquid chromatography-atmospheric pressure chemical ionization-tandem mass spectrometry (LC-ESI-MS/MS).

(3) Determination of drug concentrations in urine

[1] Timing of urine sample collection

Accumulate urine samples at the time of liver biopsy. In other words, accumulate urine samples for 24 hours from the day before the start of study drug administration (day of liver biopsy), and for 24 hours from immediately after administration at Week 8 of administration.

[2] Procedure of urine sample collection and amount of urine samples

Place each single voided urine sample obtained by natural micturition in a light-protected glass container and store in a refrigerator (4C). Combine single voided urine samples and determine the total urine volume with a glass measuring cylinder. Wash the containers with the same volume of methanol and stir the sample thoroughly. Then, dispense 200 mL each of the sample into 3 designated containers. Purge the residual space of the designated container with argon gas, and store the containers protected from light in a freezer at -80C.

[3] Shipment of the specimens

The study center will send 3 containers of the urine samples in the frozen state to the facility undertaking determination of drug concentrations for determination of drug concentrations. The facility undertaking determination of drug concentrations will keep one of the containers.

[4] Procedures for drug concentration determination

To determine the urinary concentrations of unchanged NIK-333, extract urine samples with diethyl ether/2-propanol, and determine the concentrations by liquid chromatography-ultraviolet spectrophotometry (LC-UV).

[5] Determination of metabolites in urine

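### Change from baseline in creatinine clearance is confounded with collection setting: in hospital at baseline, at home at every later time point

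*Protocol*

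**What the plan says.** Creatinine clearance is one of the blood pressure parameters. Note 3 to the schedule (section 7.3, repeated in the Summary of Study Plan) fixes when these are measured: "Blood pressure parameters will be assessed on the day of the start of administration and at Week 48 and Week 96 of administration". They are also measured when blood pressure is raised on consecutive tests. The same note fixes where the later urine is collected: "Creatinine clearance will be determined using urine samples collected at home at the timings other than the day of the start of administration".

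The baseline collection has to be pieced together from three places:

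- Section 7.3, Note 2: "Liver biopsy will be performed and blood samples and accumulated urine samples will be collected on the day before the start of administration".
- Section 4.9: "Urine sample will be accumulated for 24 hours at the time of" the biopsy, which it describes as "Liver tissues collection (during hospitalization for liver biopsy"). It also lists collections at Week 48, at Week 96 and, if possible, when blood pressure is raised.
- Section 7.6(3)[1]: "accumulate urine samples for 24 hours from the day before the start of study drug administration (day of liver biopsy"), with a second 24-hour collection from dosing at Week 8.

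Section 7.5(1)[7] marks creatinine clearance as an item to be done if possible. Section 12.3 plans lists, time-course charts and summary statistics for laboratory tests.

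**The concern.** Renal safety is a stated interest. Section 2.3 reads the phase I urine findings as "suggesting that NIK-333 affects renal functions", and the Step II rationale in section 4.4(3) names the urinary system, together with the cardiovascular system, as what is to be examined up to Week 96.

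Measured clearance depends directly on how much of the day's urine is recovered. The baseline is collected in hospital and every later value is collected by the subject at home. This switch falls between the untreated and the treated period, and Step II has no concurrent untreated group. A lost void at home would look like a fall in renal function. Over-collection at home, or an incomplete baseline, would hide one. The most exposed use is the value triggered by raised blood pressure, where a single subject's home collection would be set against that subject's inpatient baseline.

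**Working it through.** The protocol gives no figure for clearance (no expected change, SD or power; section 12.6 sets 12 subjects on feasibility), so there is nothing to reproduce. The check has two parts.

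**1. Can anything in the plan separate setting from treatment?**

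| Time point | Treatment | 24-hour urine collected | Clearance scheduled |
|---|---|---|---|
| Day before first dose | none | in hospital | yes (baseline) |
| Week 8 | 300 or 600 mg/day | in hospital | no |
| Week 48, Week 96 | 600 mg/day | at home | yes |
| Raised blood pressure | on study drug | at home | yes, if possible |
| 12 weeks after the end | none | none listed (Table 3) | no |

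To separate the two effects one would need an untreated home value, an on-drug inpatient value or an untreated group. None is scheduled. The one on-drug inpatient collection, at Week 8, is described in section 7.6(3) for drug concentration only. Week 48 and Week 96 share one setting, so that comparison is sound, but it has no untreated reference.

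**2. How large could the artefact be?** Every input here is an assumption.

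For a 24-hour collection, clearance = U × V / (P × 1440), where U and P are the urine and serum creatinine concentrations and V is the urine volume. If a fraction f of the urine is lost, the recorded clearance is (1 − f) times the true one. At an unchanged true clearance of 80 mL/min:

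- f = 0: no change
- f = 5%: 80 × 0.05 = 4 mL/min false fall
- f = 10%: 80 × 0.10 = 8 mL/min
- f = 20%: 80 × 0.20 = 16 mL/min
- f = 30%: 80 × 0.30 = 24 mL/min

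One void missed out of 5 or 6 corresponds to f = 1/5 = 20% or 1/6 = 17%. Over-collection by the same fraction reverses the sign.

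For scale, the 95% half-width of a mean paired change is t(0.975, n − 1) × SD/√n:

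| n | SD of change 10 | SD 15 | SD 20 (mL/min) |
|---|---|---|---|
| 12 | 6.4 | 9.5 | 12.7 |
| 8 (some values missing) | 8.4 | 12.5 | 16.7 |

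With 12 subjects, a shared 10% loss (8 mL/min) exceeds the half-width only at the smallest SD. A shared 20% loss (16 mL/min) exceeds it at all three. Unlike sampling error, a shared loss does not shrink with more subjects.

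**The case against.** The strongest reply is that clearance is a supplementary item, done if possible, in a descriptive analysis of 12 subjects, and that the phase I signal is covered without it. That signal was protein and occult blood in urine. Section 7.5(1)[6] measures both every 4 weeks in fresh urine, along with creatinine-corrected urinary albumin, beta-2-microglobulin, serum creatinine and urea nitrogen. None of these needs a timed collection. This stands, and it limits the point to one measure. It does not remove the point: a time-course chart of clearance will show a setting effect as a trend whether or not a test is run. It is also fair that the 80 mL/min and the loss fractions come from outside the documents, and that the effect is zero if home collections match the hospital ones.

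A reader might go further in three ways that the documents do not support.

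- **That the clearance change simply measures the switch of method, or that all renal change from baseline is spoiled.** The clearance change mixes a possible true change with a setting effect, and the other markers are untouched.
- **That baseline clearance is halved by methanol.** Section 7.6(3)[2] does say: "Wash the containers with the same volume of methanol and stir the sample thoroughly". But this is the pharmacokinetic procedure. Total volume is measured before that step, and the three containers go to the drug-concentration facility. Nothing says that creatinine is assayed from them.
- **That the baseline hormone panel must be drawn just after the biopsy.** The schedule and section 7.8 allow parameters of this kind to be taken within 14 days before the start, so an earlier draw is already possible.

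**Conclusion.** The point holds for one comparison: creatinine clearance at Week 48, at Week 96 or at a raised-blood-pressure visit against baseline. If the plan is followed exactly, that change is confounded with collection setting. The size and sign of the bias cannot be known from the documents. Under the assumptions shown, 10 to 20% under-collection gives a false fall of 8 to 16 mL/min, which is of the same order as the sampling uncertainty with 12 subjects.

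The conclusion rests on reading sections 4.9, 7.3 and 7.6(3) together to place the baseline collection in hospital. Note 3 supports that reading by exempting only the start of administration from home collection. This is a small measurement weakness in a stated safety target, worth correcting because the correction is cheap. It does not undermine the renal safety assessment as a whole.

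**What to change.** Amend sections 7.5(1)[7] and 12.3 as follows.

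- **(a) Completeness check.** Report 24-hour creatinine excretion per kg (U × V / body weight) with every clearance. Flag any home collection that differs from the subject's inpatient value by more than a percentage fixed in advance. Excretion uses quantities already needed for clearance. At steady state it reflects recovery rather than renal function, so it helps to tell lost urine from a real fall.
- **(b) Main presentation.** Show the renal trend to Week 96 mainly on clearance estimated from the 4-weekly serum creatinine with age, sex and weight, all already recorded. Keep measured clearance as supportive, and label each value with its collection setting.
- **(c) Optional.** Measure urinary creatinine in the Week 8 inpatient 24-hour urine and report it only as an early on-drug value in the same setting. It cannot stand in for the long-term comparison: half the subjects are then on 300 mg/day, and the biopsy falls 4 hours into that collection.

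The cost is some added tabulation and, for (c), about 12 urinary creatinine assays on urine already collected. No new visit or procedure is needed. The drawback of (b) is that serum-based estimates have their own error in patients with liver disease, which is a reason to show both measures.
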